## Background

Zinc is a vital micronutrient essential for protein synthesis, cell growth and differentiation, immune function, and intestinal transport of water and electrolytes.^1^ Zinc is also important for normal growth and development of children both with and without diarrhoea.^2^ Zinc deficiency is associated with an increased risk of gastrointestinal infections, altered structure and function of the gastrointestinal tract and impaired immune function.^3–5^ Dietary deficiency of zinc is especially common in low-income countries because of a low dietary intake of zinc-rich foods (including foods of animal origin) or low bioavailability due to the presence of phytates often found in cereal-based diets.^1^

The benefits of zinc supplementation in the management of diarrhoea have been observed in several studies. Patel *et al*
6 noted in a systematic review and meta-analysis an approximate 20% reduction in the mean duration of acute diarrhoea with zinc supplementation. Lazzerini and Wanzira,^7^ summarising data from 2581 children from 9 trials, noted that children older than 6 months receiving zinc supplements had a shorter diarrhoea duration by about half a day (mean difference −11.46 hours, 95% CI −19.72 to −3.19). A reduction in diarrhoea that continues up to day 7 (risk ratio 0.73, 95% CI 0.61 and 0.88) was also noted in this study. Moreover, the study indicated that zinc supplements in children with persistent diarrhoea (defined as diarrhoea for >14 days) also may shorten average diarrhoea duration by 16 hours (mean difference −15.84 hours, 95% CI −25.43 to −6.24). As a result of these and other trials, since 2005 WHO/Unicef have recommended routine zinc supplementation (10 mg daily for infants below 6 months of age; 20 mg daily for children older than 6 months) for 10–14 days.^8^

These doses, however, were not chosen after dose-ranging studies, and substantially exceed the recommended dietary allowances (RDA) for zinc in infancy and early childhood (2–5 mg/day).^9^ High doses of zinc can cause epigastric pain and lethargy, and its metallic taste can also induce vomiting. Vomiting with zinc supplements is a common side effect noted in many published trials. A meta-analysis by Lukacik *et al*

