### Sample size

We will enrol 4500 children (1500 per study arm) in the trial. Table 1 presents sample size assumptions and calculations for each of the three primary outcomes. The total sample size for the trial was selected to have at least 90% power for each of the primary outcomes. The primary outcomes (mean number of loose or watery stools postrandomisation and percentage of children with diarrhoea for >5 days) are both based on the non-inferiority hypotheses, while the primary outcome of vomiting postdose assumes a superiority hypothesis. We assumed 1:1:1 randomisation between the three treatment arms, a nominal type I error rate (α) of 0.05% and 5% loss to follow-up rate.

**Table 1 T1:** Sample size calculations for the primary trial outcomes

Outcome	Value in standard dose (20 mg/day) group	Expected value in low-dose groups	Non-inferiority margin	Power, significance level	Sample size per arm (with ~5% attrition)
Duration of diarrhoea, mean (SD)	3.0 (2.7) days	3.0 (2.7) days Lower dose equally effective	0.3 days	90%, 5%	1460
Percentage of children with diarrhoea >5 days	16%	16% Lower dose equally effective	+4%	90%, 5%	1500
Total number of loose or watery stools during follow-up, mean (SD)	10 (9) stools	10 (9) stools Lower dose equally effective	+2 stools	90%, 5%	1460
Percentage of children with vomiting during follow-up	20%	15% Lower dose safer	Not applicable because of superiority hypothesis for this outcome	90%, 5%	1340

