Total number of loose or watery stools after enrolment. An analysis of covariance (ANCOVA) approach will be used to estimate the mean differences and their 95% CI in the total number of loose or watery stools after enrolment for each lower dose arm compared with the standard dose arm, while accounting for the stratified randomisation design. The non-inferiority margin was set at two stools, therefore if the upper limit of the 95% CI is less than two stools, we will reject the null hypothesis that the lower dose zinc is inferior to the standard dose in terms of reducing the total number of loose or watery stools.

#### Primary outcome 3

Vomiting within 30 min after administration of the trial regimen. We hypothesise that the lower dose of zinc will be associated with a reduced risk of vomiting and therefore a superiority test will be used. Vomiting within 30 min of each daily zinc dose is repeatedly measured during the 14-day administration period. Generalised estimating equations (GEE) with the log link, binomial variance and exchangeable correlation matrix will be used to assess the RR of vomiting among the three treatment arms. The exchangeable working covariance matrix and robust estimators of the variances will be used to construct CIs. The robust estimators are consistent estimators of the variances even if the working correlation matrix is misspecified. Stratified randomisation factors will be considered in the model. A secondary analysis concerning severe vomiting (defined as vomiting requiring hospitalisation or vomiting requiring intravenous fluids) will also be performed in similar fashions. We will also examine the proportion of children ever vomiting between the treatment arms and examine whether the RR of vomiting differs by follow-up day.

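### Stools row of Table 1: the stated SD, margin, power and sample size do not fit together and must be reconciled with the two-stool decision rule

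*Protocol article*

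**What the plan says.** Two places in the Protocol article fix the design for this outcome.

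- **Sample size, Table 1.** The row "Total number of loose or watery stools during follow-up, mean (SD") gives mean 10 and SD 9 in the 20 mg arm and "10 (9) stools Lower dose equally effective" for the lower doses. The margin is +2 stools, with 90% power and a 5% level, and the result is 1460 per arm including about 5% attrition. The text adds equal allocation to three arms and "5% loss to follow-up rate". It says the total was chosen to give at least 90% power for every primary outcome.
- **Analysis of primary outcomes, Primary outcome 2.** "The non-inferiority margin was set at two stools", and the null hypothesis of inferiority is rejected "if the upper limit of the 95% CI is less than two stools".

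The duration row of Table 1 also prints 1460 per arm, for mean 3.0 days, SD 2.7 and a margin of 0.3 days at the same power and level.

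**The concern.** For a difference in means with no true difference expected, the sample size depends on the margin and the SD only through their ratio. The duration row has margin/SD = 0.3/2.7 = 1/9. The stools row has 2/9. Doubling the ratio must divide the sample size by four, yet both rows print 1460, so at least one entry in the stools row cannot belong with the others.

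One of the entries in doubt is the threshold on which a primary outcome will be judged. If the margin is the misprint, the error also sits in the decision rule and changes what can be called non-inferior. If the sample size or the SD is the misprint, the rule stands, but the stated power or variability is wrong.

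**Working it through.** **Inputs.** SD 9, margin 2 stools, true difference 0, 90% power, 5% level, 5% attrition and 1500 enrolled per arm, all from Sample size and Table 1. The 95% confidence interval rule is from Primary outcome 2. Sidedness is not stated, so both readings are shown. The text prints "a nominal type I error rate (α) of 0.05" followed by a percent sign; I take 5%, as in Table 1.

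**Formula.** Evaluable per arm: n = 2 × (SD/margin)² × (z_α + z_β)². Enrolled per arm: n / 0.95. With unrounded normal quantiles, (z_α + z_β)² is 8.564 at one-sided 5% and 10.507 at one-sided 2.5%.

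**Step 1: find the table's convention from the other non-inferiority rows.**
- Duration: 2 × (2.7/0.3)² × 8.564 = 1387.3; /0.95 = 1460. Printed: 1460.
- Diarrhoea beyond 5 days: 2 × 0.16 × 0.84 × 8.564 / 0.04² = 1439; /0.95 = 1515. Printed: 1500.

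Both fit one-sided 5%.

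**Step 2: try to reproduce the stools row.**

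| Margin | One-sided level | Evaluable per arm | Enrolled per arm |
|---|---|---|---|
| 2 stools | 5% | 2 × (9/2)² × 8.564 = 346.8 | 365 |
| 2 stools | 2.5% | 2 × (9/2)² × 10.507 = 425.5 | 448 |
| 1 stool | 5% | 2 × 9² × 8.564 = 1387.3 | 1460 |

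With a 2-stool margin the printed figure is 3.3 to 4 times too large (1460/448 and 1460/365). Even reading the level literally as 0.05% gives only 892 (one-sided) or 968 (two-sided) with attrition.

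**Step 3: what would explain 1460.**
- A margin of 1 stool at one-sided 5%. At one-sided 2.5% and 1387 evaluable, the implied margin is 3.2415 × 9 × √(2/1387) = 1.11 stools.
- An SD of 18 with a 2-stool margin, which has the same ratio of 1/9.
- A sample size carried over from the duration row.

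**Step 4: what the rule does as written.** Evaluable per arm: 1500 × 0.95 = 1425. SE = 9 × √(2/1425) = 0.337, and the 95% half-width is 0.66. The largest observed excess that passes is 2 − 0.66 = 1.34 stools. The probability of declaring non-inferiority at a true excess d is Φ((margin − d)/0.337 − 1.96):

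| True excess (stools) | Margin 2 | Margin 1 |
|---|---|---|
| 0 | 99.996% | 84% |
| 0.5 | 99.4% | 32% |
| 0.9 | 90% | 4.8% |
| 1.0 | 84% | 2.5% |
| 1.5 | 32% | below 0.1% |
| 2.0 | 2.5% | below 0.1% |

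If the true SD were 18, a 2-stool margin would give 84% power at no difference, and a dose 1 stool worse would pass 32% of the time.

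**The case against.** The strongest reply is that the margin is the best-attested entry. Two stools appears in both Table 1 and the decision rule, while 1460 appears once for this outcome and is identical to the figure in the duration row, so a copied sample size is at least as plausible as a wrong margin. The pattern of a margin at 10% of the mean comes only from mean duration, which is not listed under Outcome measures as a primary outcome. The other non-inferiority primary outcome uses 4 points on 16%, or 25% of the reference value, and two stools on 10 is 20%. All of this stands. A reader might infer that the trial was sized for 1 stool and that the rule must be changed to it; the document does not establish that.

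Nor does the row set enrolment. Correcting it to 365 would still leave 1500 per arm, the same SE and the same pass probabilities. Surplus power is not a defect, and the error rate at a true excess of exactly 2 stools remains 2.5%. This also stands. A reader might infer that the test is a foregone conclusion. That is too strong: a pass is near-certain only for small true differences, and it falls to 32% at 1.5 stools.

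A reader might also infer that two stools would give away most of the benefit of zinc. The Background cites an "approximate 20% reduction in the mean duration of acute diarrhoea with zinc supplementation". If that carried over to stool counts, the mean without zinc would be 10/0.8 = 12.5 stools, the whole effect 2.5 stools, and the margin 2/2.5 = 80% of it. But the cited effect is on duration, and the document gives none for stool counts, so the conclusion rests on that assumption alone. The clinical rationale for the margin may lie in the full protocol, which is not shown.

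None of these replies makes the row consistent. The article itself prints inputs and a result that disagree.

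**Conclusion.** The stated sample size and power for primary outcome 2 are wrong as written. SD 9, a 2-stool margin and 90% power call for about 365 or 448 per arm, depending on sidedness, and not 1460. Taking SD, margin and enrolment as printed, the power at no difference is above 99.9% rather than 90%.

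Which entry is wrong cannot be settled from the document. The exact match to a 1-stool margin depends on a one-sided 5% level, whereas the decision rule works at one-sided 2.5%. The pass probabilities assume SD 9, 5% loss and a normal approximation without any precision gained from covariate adjustment. The practical stake is how strict the conclusion on stool count will be: a dose truly 1 stool worse passes 84% of the time under a 2-stool margin and 2.5% of the time under a 1-stool margin.

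**What to change.** Before unblinding, retrieve the original calculation and reconcile margin, SD and sample size in Table 1 with the rule under Primary outcome 2. Then:

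- **If two stools and SD 9 were intended:** correct the row to about 365 per arm (one-sided 5%) or 448 (one-sided 2.5%), name the sidedness, and state power above 99.9% with 1500 enrolled per arm.
- **If 1 stool was the margin used for sizing:** correct both Table 1 and the decision rule to it, state about 84% power under the 95% confidence interval rule, and amend the claim of at least 90% power for each primary outcome.
- **If the SD was misprinted:** print the SD actually used. At SD 18 the margin stays at two stools, power under the 95% confidence interval rule is about 84%, and the 90% claim needs the same amendment.

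The cost is a dated wording change and no extra children: the outcome of diarrhoea beyond 5 days sets the 1500 per arm. Under the second and third outcomes the price is an openly lower stated power. Because Trial status puts the end of follow-up at about April 2019, any change to the margin should be documented as made blind and traced to the original calculation.

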### Analysis of change in plasma zinc and other secondary outcomes

Due to the sampling design of participants having paired blood sampled on three schedules (days 1 and 15; days 3 and 21; days 7 and 30), we will assess the effect of the randomised zinc regimen at both the population level and individual level. For the analysis of population-level zinc, we will use a mixed model approach to compare patterns of plasma zinc concentrations over time between the randomised treatment arms. The main exposure variables in the model will include treatment arm, study day and an interaction term between treatment arm and study day. In case there is not a linear relationship between study day and plasma zinc concentrations, restricted cubic splines will be used to examine the non-linear relationship between these two variables. The interaction term between zinc dose and study day in the model measures whether the trajectory of plasma zinc differs by zinc supplementation over the full period. If the overall test for this interaction term is statistically significant, group means at each assessment day will then be compared using least-square means with the Tukey-Kramer adjustment. To be consistent with our stratified randomisation study design, stratification factors will be included in the model.

For all other secondary outcomes (see clinicaltrial.gov NCT03078842), we will use approaches similar to the primary analyses, including an ANCOVA approach for non-repeated continuous outcomes, RR regression for non-repeated binomial outcomes and GEE or mixed effect models for repeated longitudinal outcomes.

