### Primary and secondary objectives

The overall aim of ZTDT is to identify the optimal dose of zinc in children under 5 years with acute diarrhoea.

The primary aims of the study are: (1) to assess whether lower doses of zinc (5 or 10 mg/day) are at least as effective as the standard dose of zinc (20 mg/day) in children aged 6–59 months, in terms of burden of illness (percentage of subjects with diarrhoea lasting >5 days; mean number of loose or watery stools during follow-up) and (2) to evaluate the improved effectiveness by reduction in the risk of vomiting in 30 min after receipt of the supplement in low-dose supplemental zinc (5 or 10 mg/day) in comparison to standard dose of zinc (20 mg/day).

Secondary aims of the study are: (1) to explore whether lower doses of zinc have any impact on postacute illness morbidity outcomes assessed at 30, 45 and 60 days, (2) to explore whether duration of treatment, estimated by mother’s reports and collection of used zinc blister packs, has any impact on the primary outcomes, (3) to determine the acceptability of low-dose supplemental zinc compared with standard zinc dose based on an acceptability scale and (4) to determine whether the different doses of zinc are associated with differential plasma zinc levels at days 3, 7, 15, 21 and 30 after randomisation.

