### Interventions

Children are randomised to receive one of the three zinc sulfate regimens (each taken once daily for 14 days): (1) 5 mg; (2) 10 mg or (3) 20 mg. The zinc tablet (all three regimens) ingredients include aerosil, maize starch, ethylvanillin (a vanilla flavour), aspartame, magnesium stearate vegetal and vivapur. The three study tablets have identical appearance, taste and smell. The supplement is a dispersible tablet that dissolves in water or breast milk in about 20 s. The caretakers are instructed to dissolve the tablet in 5–10 mL of water or breast milk immediately before administration. Children receive zinc supplementation for 14 days. The first dose of study drug is given at the health facility in which the child is enrolled.

All three doses of the regimen are packaged identically; 10 tablets in 1 blister, 2 blisters in 1 pack (extra doses are provided for redosing in case of vomiting). Each pack is prelabelled with participant ID. Study regimen is manufactured by Laboratoires Pharmaceutiques Rodael, France and shipped to WHO for randomisation and labelling, before shipment to recruitment sites (as described in ’Randomisation, allocation, concealment and masking' section).

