### Blood sampling and laboratory investigations

To allow the measurement of the potential differential impact of the varying zinc doses on plasma zinc levels during the follow-up period, each study participant will provide two blood samples. One-third of the study participants will have blood draws at days 1 and 15, one-third at days 3 and 21 and the remaining one-third on days 7 and 30 postenrolment for assessment of plasma zinc levels.

Blood drawing will follow the protocols of the International Zinc Nutrition Consultative Group (IZINCG). These include use of powder-free gloves, zinc-free syringes and butterfly, needles and trace element-free blood tubes.^14^ Plasma is separated at 15 min after blood collection and aliquots are transferred into trace element-free Eppendorf plastic tubes for temporary storage at −20°C and then shipped to central lab for final storage at −80°C in India. In Tanzania, plasma samples are stored in site refrigerators at 2°C–8°C and then shipped to central laboratory storage at −80°C by the end of the day. Plasma zinc concentrations will be measured by atomic absorption spectroscopy (AAS-400 PerkinElmer, USA).

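### Plasma zinc differences at named days are to be read from a curve in continuous study day running across the end of dosing, so they can be materially biased; a categorical day factor avoids this

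*Protocol article*

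**What the plan says.** The protocol article (Analysis of change in plasma zinc and other secondary outcomes) specifies a mixed model for the population-level analysis: "The main exposure variables in the model will include treatment arm, study day and an interaction term between treatment arm and study day". On the shape over time it adds "In case there is not a linear relationship between study day and plasma zinc concentrations, restricted cubic splines will be used"; the stated purpose is to describe how zinc varies with day, and arm is not mentioned. Of the interaction, taken across all study days, it says "The interaction term between zinc dose and study day in the model measures whether the trajectory of plasma zinc differs by zinc supplementation". If that test is significant, "group means at each assessment day will then be compared using least-square means with the Tukey-Kramer adjustment".

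The design around this model is fixed elsewhere in the article:

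- Blood sampling and laboratory investigations: "One-third of the study participants will have blood draws at days 1 and 15, one-third at days 3 and 21". The last third is sampled on days 7 and 30.
- Interventions: "Children receive zinc supplementation for 14 days".
- Primary and secondary objectives, aim 4: whether the doses are associated with "differential plasma zinc levels at days 3, 7, 15, 21 and 30 after randomisation". Day 1 is not in this aim; it appears in the list of secondary outcomes.

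**The concern.** A provision for departure from linearity makes sense only if study day is continuous, so the default is a straight line. A least-square mean at a given day is then a prediction from the curve, not an estimate from that day's samples.

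Two of the six days (3 and 7) fall during dosing. Day 15 is the day after dosing ends, and days 21 and 30 are 7 and 16 days after the fourteenth day. A dose difference that builds up and then fades is foreseeable from the schedule alone. A line cannot rise and fall, and a smooth spline with few knots carries signal across the point where dosing stops.

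Aim 4 asks about named days. Statements on how soon the dose groups separate, and whether a difference persists after treatment, could then reflect the choice of curve as much as the data.

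**Working it through.** **No stated figure to reproduce.** The article gives no plasma zinc trajectory, SD or within-child correlation. Those below are assumptions.

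**Inputs from the article.** There are 1500 children per arm, three sampling schedules of one-third each, and 5% loss to follow-up. Per arm and day: 1500/3 = 500, and 500 × 0.95 = 475.

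**Assumed arm differences** at days 1, 3, 7, 15, 21, 30, with the peak scaled to 1 and zero on day 1:

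- A, rise and plateau: 0, 0.6, 1, 0.9, 0.3, 0
- B, peak at day 15: 0, 0.14, 0.43, 1, 0.4, 0.1
- C, abrupt on and off: 0, 1, 1, 1, 0, 0
- D, slow decay: 0, 0.4, 0.8, 1, 0.8, 0.5

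**Method.** Project each profile on the model's time terms by least squares. The fitted value at a day is what the model estimates there in expectation.

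**Linear arm-by-day term, profile C by hand** (equal weight per day):

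- Mean day = 77/6 = 12.83; mean difference = 3/6 = 0.5.
- Sum of squared deviations of day = 636.8.
- Cross-product = (3 + 7 + 15) − 3 × 12.83 = −13.5.
- Slope = −13.5/636.8 = −0.0212.
- Day 1: 0.5 − 0.0212 × (1 − 12.83) = 0.75, where the truth is 0.
- Day 15: 0.5 − 0.0212 × (15 − 12.83) = 0.45, where the truth is 1.

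All four profiles, same method (fitted value, truth in brackets):

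| Profile | Day 1 | Day 15 | Day 30 |
|---|---|---|---|
| A | 0.60 (0) | 0.44 (0.9) | 0.27 (0) |
| B | 0.28 (0) | 0.36 (1) | 0.43 (0.1) |
| C | 0.75 (0) | 0.45 (1) | 0.14 (0) |
| D | 0.42 (0) | 0.61 (1) | 0.82 (0.5) |

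So day 1 is overstated by 0.28 to 0.75 and day 15 understated by 0.39 to 0.64. With a correlation of 0.5 between a child's two samples, the day 1 range is 0.24 to 0.78 and the day 15 range is unchanged.

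**Spline for the overall time course, linear arm interaction.** The arm difference is still intercept plus slope times day, so the table above applies in full.

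**Spline crossed with arm.** Error at each day, zero correlation, over knot sets 1/5/15/30, 1/5/18/30, 1/7/15/30, 1/3/7/15/30 and 1/7/15/21/30:

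| Profile | Day 1 | Day 15 | Day 21 |
|---|---|---|---|
| A | 0.01 to 0.08 | −0.12 to −0.01 | 0.00 to 0.11 |
| B | −0.05 to 0.02 | −0.24 to 0.00 | 0.00 to 0.22 |
| C | 0.04 to 0.23 | −0.34 to −0.04 | 0.01 to 0.32 |
| D | 0.00 to 0.04 | −0.03 to −0.01 | 0.00 to 0.03 |

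With correlation 0.5, the largest absolute day 1 error is 0.11 for A, B and D and 0.23 for C; the largest error at any day is 0.25 and 0.42 respectively. For B and C the day 15 and 21 errors are about 0.2 to 0.3 with most knot sets, and much smaller only when knots sit at both 15 and 21. With three knots the day 1 error runs from −0.07 to 0.50.

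**Categorical day crossed with arm.** The error is 0 at every day for every profile, because each arm-day mean has its own parameter.

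**Precision.** For categorical day, the SE of an arm difference is √(2/475) = 0.065 SD. For the line it is about 0.03 to 0.05 SD. At an assumed peak of 0.2 SD and correlation 0.5, the day 1 artefact of the line is 1.2 to 4.0 of its own SEs.

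**The case against.** The strongest reply is that the plan sets the line aside in just the situation assumed here: if the relation is not linear, splines are used. For profile C with 475 per arm and day, and ignoring correlation, the lack of fit of the line in the arm difference has noncentrality of about 0.25 × 1.22/(2/475) = 72 on 4 degrees of freedom at a peak of 0.5 SD, and about 12 at 0.2 SD (1.22 is the sum of squared errors of the line). It would almost certainly be seen in the first case and probably in the second. Splines with 4 or 5 knots crossed with arm then leave little on day 1 for smooth profiles. An overall test of the interaction followed by means at each assessment day is also compatible with a multi-degree-of-freedom spline-by-arm term. Knots and coding are details that an article commonly leaves to the analysis plan, which is not shown.

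Much of this stands. A reader might infer that the day-specific differences are simply wrong and that a false day 1 difference will be reported. The article does not support that. The spline provision exists, and spline-by-arm terms are not excluded. A day 1 difference is false only if the sample precedes the first dose or no early effect exists. The first dose is given at the enrolling facility, but the order of draw and dose is not stated. The use of baseline plasma zinc as an effect modifier suggests a pre-dose draw without settling it.

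The reply does not remove two things. The stated trigger and the spline concern day against zinc, not the shape of the arm difference, and nothing says that the spline terms enter the interaction. And fully crossed splines still misstate days 15 and 21 for sharper profiles. Missing knots are not the fault; the fault is the stated choice of a continuous curve to answer questions about six fixed days.

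**Conclusion.** The point holds in a conditional form. The plan takes arm differences at named days from a continuous curve that spans the end of dosing, and these can be materially biased. The linear form, or a spline without arm interaction, carries about 0.3 to 0.75 of the peak difference to day 1 where the truth is zero and understates day 15 by about 0.4 to 0.64. With 4 to 5 knots crossed with arm, the day 1 problem largely disappears for smooth profiles. Errors of about 0.2 to 0.3 at days 15 and 21 remain possible for sharper ones, and somewhat more for an abrupt profile with correlated samples.

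These sizes rest on assumed trajectories with no difference on day 1, equal numbers per day and the knot sets listed. They show what the model can do, not what it will do. The outcome is secondary: no primary outcome, margin or sample size is touched. The change is worth making because it costs little.

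**What to change.** For the comparisons at named days, fit study day as a six-level categorical factor (1, 3, 7, 15, 21, 30) with arm-by-day terms, a child-level random effect and the stratification factors. Take the day-specific arm differences from this model and keep splines for displaying the time course. State whether the day 1 sample is drawn before the first dose; if it is, constrain the arms to a common mean on day 1.

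The cost is wording and some precision. With three arms and both arm and day main effects in the model, the interaction has 2 × 5 = 10 degrees of freedom instead of 2 × 1 = 2 for a linear term. The SE of a day-specific difference is about 0.065 SD, against about 0.03 to 0.05 SD for the line. With about 475 to 500 children per arm and day this is affordable. No change to sampling or data collection is needed.

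### Plasma zinc levels are compared by day only after a significant arm-by-day interaction, which tests trajectory rather than the level difference in secondary aim 4

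*Protocol article*

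**What the plan says.** Under *Primary and secondary objectives*, the fourth secondary aim is "to determine whether the different doses of zinc are associated with differential plasma zinc levels at days 3, 7, 15, 21 and 30". This is a question about levels on named days.

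Under *Analysis of change in plasma zinc and other secondary outcomes*, the population-level analysis is a mixed model: "The main exposure variables in the model will include treatment arm, study day and an interaction term between treatment arm and study day". The article says that the interaction "measures whether the trajectory of plasma zinc differs by zinc supplementation over the full period". On the coding of day it says: "In case there is not a linear relationship between study day and plasma zinc concentrations, restricted cubic splines will be used". The decision rule is: "If the overall test for this interaction term is statistically significant, group means at each assessment day will then be compared". Those comparisons are to be Tukey-Kramer adjusted. No step is given for a non-significant interaction, and no test of the arm term is described.

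The same section also says that "we will assess the effect of the randomised zinc regimen at both the population level and individual level", but gives no method for the individual level.

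**The concern.** The contrasts that answer aim 4 depend on a test of a different hypothesis. Arms can differ in level on every day that aim 4 names and still run close to parallel. The interaction is then likely to be non-significant, and the written rule ends without a dose comparison on any day. A reader of the trial report could then be told that trajectories did not differ, with no estimate of the dose difference in plasma zinc, although the doses do differ.

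**Working it through.** The article states no power or expected difference for plasma zinc, so there is no figure to reproduce. The check is how often the gate opens when the doses truly differ.

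**Inputs from the article**
- 1500 children per arm and 5% loss to follow-up (*Sample size*).
- Three paired sampling schedules, days (1, 15), (3, 21) and (7, 30), with one-third of children on each (*Blood sampling and laboratory investigations*). This gives 1500/3 × 0.95 = 475 per arm per schedule.
- Significance level 5%, as in Table 1.
- Dosing for 14 days (*Interventions*).

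**Assumptions, not in the article**
- Within-child correlation ρ = 0.3 to 0.6.
- Difference δ between 20 mg and 5 mg in SD units, linear in dose. The arm means are then δ, δ/3 and 0 for 20, 10 and 5 mg.
- Spline knots at days 1, 7, 15 and 30.

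**Method.** Power of the Wald test is P(χ²(df, λ) > 95th percentile of χ²(df)), where λ is the noncentrality from the generalised least squares information. The interaction has 2 df with linear day, 6 df with the 4-knot spline and 10 df with categorical day. The comparator is a 10-df joint test of any arm difference on days 3 to 30.

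**Pattern A: the same difference on all six days.** The curves are parallel, so λ = 0 for every coding and every δ. The gate opens 5% of the time and stays shut 95% of the time.

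**Pattern B: no difference on day 1, constant δ on days 3 to 30.** The sum of squares of the arm means about their average is δ²(10/9 − 16/27) = δ² × 14/27. Let K = 475 × δ² × 14/27. At δ = 0.2, K = 9.85.
- Categorical interaction: λ = K[1/(1−ρ²) − 1/(6(1+ρ))]. At ρ = 0.3 this is 9.85 × 0.971 = 9.56, power 52%. At ρ = 0.6 it is 9.85 × 1.458 = 14.37, power 74%.
- Direct joint test: λ = K[1 + 4/(1+ρ)]. At ρ = 0.3 this is 9.85 × 4.077 = 40.17, power 99.8%. At ρ = 0.6 it is 9.85 × 3.5 = 34.48, power 99.4%.
- Linear and spline coding were computed numerically from the same information matrix. At ρ = 0.3, λ = 2.22 and 7.28. At ρ = 0.6, λ = 3.00 and 11.75.

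**Pattern C: no difference on day 1, constant δ on days 3 to 15, none on days 21 and 30.** This represents fading once dosing ends.

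Chance that the gate opens, over ρ = 0.3 to 0.6:

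| Pattern, δ | Linear day | 4-knot spline | Categorical day | Direct joint test |
|---|---|---|---|---|
| A, 0.2 SD | 5% | 5% | 5% | over 99% |
| B, 0.1 SD | 9–11% | 14–20% | 14–19% | 47–54% |
| B, 0.2 SD | 25–32% | 49–73% | 52–74% | over 99% |
| B, 0.3 SD | 50–64% | 88–99% | 92–99% | about 100% |
| C, 0.2 SD | 45–72% | 88–99% | 91–99.6% | 98.8–99.9% |
| C, 0.3 SD | 81–98% | about 100% | about 100% | about 100% |

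**The case against.** **Flat pattern.** The 95% figure needs full separation by day 1 and no change to day 30. Days 15, 21 and 30 all follow the last scheduled dose, so build-up or fading is plausible, and either one is itself an interaction. This stands: the 5% result is the extreme case, not the expected one.

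**Day 1 as baseline.** Aim 4 leaves out day 1, and *Sensitivity analyses and modification of treatment effect* lists baseline plasma zinc as an effect modifier, for which day 1 is the only candidate sample. A steady shift after day 1 would then show as interaction. The article does not settle this. It counts draw days from enrolment, lists day 1 among the outcome days, and says "The first dose of study drug is given at the health facility in which the child is enrolled" without timing the blood draw. Pattern B grants the baseline reading and still shows a clear loss at 0.2 SD.

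**Aim 4 left unanswered.** A reader might infer that the aim goes unanswered, or that a steady dose difference would usually go untested. The article does not support either. The arm term is in the model, an individual-level analysis is announced, and an analysis plan that is not shown may specify both. Neither closes the gap as published, however. With uncentred linear day, the arm coefficient is the difference extrapolated to day 0, not a contrast on an aim 4 day. An analysis of within-child change would cancel a difference present equally at both draws.

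**Like for like.** The direct test pools days, whereas the gate controls single-day Tukey contrasts. With 475 per arm the SE is √(2/475) = 0.0649 SD and the Tukey critical value is 2.344. Power on one day is then about 77% for 20 versus 5 mg (0.2 SD) and about 39% for 20 versus 10 mg (0.133 SD). This stands: ungating gives each single-day contrast that power, not 99%.

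**Multiplicity.** Testing an interaction before many pairwise contrasts is a common safeguard, and this is a secondary biomarker. But the Tukey-Kramer adjustment already covers the pairwise comparisons within a day, and a joint test of level would guard across days without changing the question.

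**Conclusion.** The point holds in a limited form. The stated gate tests trajectory while aim 4 asks about level, so the rule can withhold the aim 4 contrasts when the doses differ. The size depends on the pattern, and every effect size, correlation and knot position used here is an assumption.
- The loss is near total for a difference that is flat from day 1.
- It is large for a steady 0.2 SD difference after day 1 if day is linear, and moderate to large with flexible coding.
- It is small at 0.3 SD with flexible coding, or where the difference fades after dosing and day is coded flexibly.

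To say that the interaction test loses most of the power would be fair only for the flat pattern, or for linear day at about 0.2 SD or less. The primary conclusions on diarrhoea and vomiting are not affected.

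**What to change.** State that each low-dose minus 20 mg difference in plasma zinc will be estimated on days 3, 7, 15, 21 and 30, with Tukey-Kramer adjusted 95% CIs, whatever the interaction result. If a gate is wanted, use one joint test of any arm difference over days 3 to 30. Keep the arm-by-day interaction as a supportive analysis of trajectory. The change is one of wording and needs no new data. The cost is a few more adjusted contrasts to report.
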